### Interventions

#### Surgical treatment

Surgical interventions for CLBP in this study are fusion (anterior and posterior lumbar interbody fusion, posterolateral instrumented fusion) and nonfusion surgery (decompression, dynamic stabilization, total disc replacement). Given the nature of interventions, a sham intervention is not feasible.

#### Conservative treatment and co-interventions

We defined the absence of a surgical treatment as conservative treatment. Different conservative treatments are considered as co-interventions. These co-interventions that also can be applied to the surgical patient group are biomedical, psychologically oriented (cognitive behavioural therapy), and socio-occupational interventions (return-to-work program). Biomedical interventions include physical treatments, exercise therapy, manual therapy, back schools, pharmacological procedures (analgetics, NSAID, opioids, antidepressants), and invasive nonsurgical treatments (acupuncture, injections, facet/nerve root blocks, neuroreflexotherapy, percutaneous electrical nerve stimulation, radiofrequency, intradiscal electrothermal therapy, intradiscal radiofrequency thermocoagulation, cryotherapy of the facets, alcohol denervation, temporary epidural catheters, permanent intrathecal pain-control pumps, and spinal cord stimulators).

### Outcome assessment

#### Demographic and baseline characteristics

The following demographic and baseline characteristics will be collected by patient self-assessment: gender, age, comorbidity (SCQ), marital/relationship status, smoking behaviour, onset/duration/recurrence of LBP, number/level of previous spine surgeries, duration of previous conservative treatment, educational/work/disability compensation status, work history, biomechanical workload, duration of work-absenteeism, job satisfaction, work stress factors, job control, social recognition of LBP from supervisors and colleagues, pain tolerance during work, belief that work has caused LBP, recovery/emotional distress after work, social stress factors, search for social support, condition-specific disability (ODI), general physical and mental health (SF-36), cost-utility of treatment (index based on EQol-5D in combination with cost data), intensity of back and leg pain (VAS), pain frequency, location and number of other painful body sites (SEQ pain assessment), pain behaviour, pain control, self-efficacy, family reinforcement of pain, interference of LBP with work and/or activity, symptom-specific well-being, general well-being, somatisation (MSPQ), depression (ZUNG), fear avoidance beliefs (FABQ), coping strategies (CSQ), and patients' expectations.

Physician-based assessment of patient characteristics at baseline include centre/clinic of treatment, in/outpatient treatment, height, weight, and medication.

#### Outcome measures

Relevant outcomes are identified as scores organised in categories of answers in standardised multi-dimensional assessment tools. Significance of outcomes is defined by effect sizes (i.e. differences between treatment groups in changes from baseline to endpoint, typically divided into three groups: short-, medium-, and long-term changes of respective scores). For this study, outcome measures will be assessed at six-month follow-up. Longer follow-ups may result in difficulties for the identification of effect modifiers [23].

ODI [24,25], SF-36 [26], EQol-5D [27], and pain measured by VAS [28] are among the most frequently used outcome assessment measurements of CLBP. All of them are valid and reliable. In this study, the primary endpoint at six-month follow-up is ODI. Key secondary endpoints are SF-36, EQol-5D, and VAS.

Other secondary outcomes that will be collected by patient self-assessment are onset/duration/recurrence of LBP [29-31], work/disability compensation status [32,33], duration of work-absenteeism [34], location and number of other painful body sites [35,36], interference of LBP with work and/or activity, symptom-specific well-being, general well-being, and satisfaction with treatment.

Physician-based assessment of secondary treatment outcomes at six-month follow-up include rate/type/therapeutic consequences of complications [37], change in medication, and overall outcome (McNab criteria).

Given the nature of interventions, blinding is not feasible. Outcome assessments are based on standardised, reliable, valid tools.

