#### Effect modification

Possible effect modifiers are all co-interventions, as well as all demographic and baseline characteristics [23,38-40], which include gender [41], age [42], severity of pain [43], comorbidity [44], socioeconomic status [45], work-related factors [34,46,47], indirect reward parameters due to the health care system [48], psychosocial distress [49-52], somatisation and depression [53,54], fear-avoidance beliefs and coping strategies [55,56], and expectations [57].

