### Statistical Analysis

#### Outcomes

In this prospective cohort study, two interventions for CLBP are compared: surgical and conservative treatment. Subgroups of different surgical treatments can be distinguished. Nonsurgical co-interventions may have an effect on patient groups with surgical as well as with conservative treatment.

Follow-up data at six months will be analysed according to the intention-to-treat principle, except for those patients who change treatment groups before the beginning of the allocated treatment.

Changes in dependent outcome variables between baseline and follow-up at six months will be analysed by multiple linear regression models. Surgical and conservative treatment, patient characteristics, and co-interventions are independent variables. To address potential effect modification, we will then incorporate interactions between type of treatment and the different co-interventions and patient characteristics.

Highest priority among co-interventions will be given to the analysis of effects of cognitive behavioural therapy and return-to-work programs. Among patient characteristics highest priority in data analysis will be given to gender, age, and duration of work-absenteeism.

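### As written, the regression for change in medication adjusts for drug use after the start of treatment, which overlaps that outcome

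*Protocol article*

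**What the plan says.** Drug use appears in three roles in the protocol article.

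- **Outcome.** Outcome measures lists, among the physician-based secondary outcomes at six months, "change in medication, and overall outcome (McNab criteria").
- **Co-intervention.** Conservative treatment and co-interventions includes "pharmacological procedures (analgetics, NSAID, opioids, antidepressants") among the biomedical co-interventions. They are not confined to one group: "These co-interventions that also can be applied to the surgical patient group" is how that section introduces them.
- **Baseline characteristic.** Demographic and baseline characteristics has the physician record "centre/clinic of treatment, in/outpatient treatment, height, weight, and medication".

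The analysis rule is under Statistical Analysis, Outcomes: "Changes in dependent outcome variables between baseline and follow-up at six months will be analysed by multiple linear regression models". The regressors follow: "Surgical and conservative treatment, patient characteristics, and co-interventions are independent variables". Interactions of treatment with co-interventions and patient characteristics are then added, and the Effect modification section widens the candidates: "Possible effect modifiers are all co-interventions", along with the baseline characteristics. No sentence exempts an outcome or a co-intervention from this rule.

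**The concern.** A covariate measured after treatment starts, and which treatment can change, takes part of the treatment effect out of the treatment coefficient. Here the problem is sharper than usual, because the covariate (drugs taken after baseline) and the outcome (change in drugs since baseline) draw on the same behaviour and possibly on the same record. An analyst who applies the stated rule to change in medication would report a treatment coefficient that does not answer whether drug use fell more after surgery or after conservative care. The treatment-by-drug interaction has the same defect. At stake is the interpretation of one named secondary outcome.

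**Working it through.** The plan gives no figure for this outcome, so there is none to reproduce. The check is algebra plus an example with assumed rates.

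**Notation.** T = 1 for surgery, 0 for conservative care. B = drug use at baseline. F = drug use at six months. Outcome Y = F - B. A = the drug co-intervention as coded.

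**Assumed inputs (none is in the document).** Use at baseline is 70% in both groups and unrelated to later use. Six-month use is f1 = 0.40 after surgery and f0 = 0.60 after conservative care. Groups are equal in size, a simplification the sample size section also makes. Anyone using drugs at six months counts as a user during follow-up.

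**True contrast.** (0.40 - 0.70) - (0.60 - 0.70) = -0.30 + 0.10 = -0.20. A model with T and B only returns this value.

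**Case 1: A is the six-month record (A = F).** Y = 0·T - 1·B + 1·F holds for every patient. The fit is perfect and the treatment coefficient is 0.00, whatever the rates are. The treatment-by-drug interaction is zero for the same reason.

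**Case 2: A is any use during follow-up, with rates a1 (surgery) and a0 (conservative).** Within a group, cov(F, A) = f(1 - a) and var(A) = a(1 - a). The pooled within-group slope of F on A is

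s = [f1(1 - a1) + f0(1 - a0)] / [a1(1 - a1) + a0(1 - a0)],

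and the treatment coefficient is -0.20 - s × (a1 - a0).

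For 94% v 74%: s = (0.024 + 0.156) / (0.0564 + 0.1924) = 0.1800 / 0.2488 = 0.723, so the coefficient is -0.20 - 0.723 × 0.20 = -0.34. A simulation of 200,000 patients gave -0.3445.

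| Any use, surgery v conservative (assumed) | s | Treatment coefficient |
|---|---|---|
| 94% v 74% | 0.723 | -0.34 |
| 94% v 84% | 0.629 | -0.26 |
| 80% v 74% | 0.670 | -0.24 |
| 95% v 90% | 0.582 | -0.23 |
| 94% v 94% | 0.532 | -0.20 (no bias) |
| 70% v 74% | 0.686 | -0.17 |

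Since s is positive, the bias takes its direction from a1 - a0: away from zero if drug exposure is higher after surgery, towards zero if it is lower, none if it is equal.

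**Check under a different assumed model.** A continuous drug score was simulated with a true treatment effect of -0.5 (error SD 1), n = 792 (the number the protocol expects to analyse) and 500 runs. The mean treatment coefficients were:

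- baseline score only: -0.50
- baseline plus a yes/no indicator of follow-up use: -0.35 (31% smaller)
- baseline plus a noisy measure of use during treatment: -0.24 (53% smaller)
- baseline plus the follow-up score itself: 0.00, with R-squared 1.00

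In this model the partial overlaps all shrink the effect, whereas most rows of the table exaggerate it. Size and direction therefore depend on the coding and the rates.

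**The case against.** The strongest reply is that the analysis paragraph is a template. It never names medication, and the abstract ties the regression to change in ODI. It cannot literally govern every listed outcome, since complications and satisfaction with treatment have no baseline value from which to form a change. Priority among co-interventions goes to cognitive behavioural therapy and return-to-work programmes, and an unseen analysis plan may drop drug terms where they make no sense.

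Part of this stands. The article does not say how the drug co-intervention is coded, and a fuller document could remove the overlap. But change in medication does have a baseline, the rule is stated for outcome variables in the plural, and giving priority to other co-interventions does not remove drugs from the list. An analysis plan that follows the rule inherits the problem.

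Three stronger readings go too far:

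- **A reader might infer that the plan explains drug use by drug use and can show no treatment effect on it.** That is exact only when regressor and outcome come from the same six-month record, which the document does not say.
- **A reader might infer that any other coding must bias the result, and in a known direction.** With equal drug exposure in both groups, the example shows no bias. With unequal exposure, the direction depends on which group has more.
- **A reader might count baseline medication as part of the fault.** It precedes treatment and is a proper covariate.

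**Conclusion.** The point holds in a limited form. The stated rule conditions change in medication on drug use after baseline. The coefficient is then zero by identity if the same record is used. Otherwise it is not the total treatment effect: against a true contrast of -0.20, the assumed scenarios with any use during follow-up run from about -0.17 to -0.34 and include one with no bias. Only the identity is free of assumptions; the other figures rest on the assumed rates, equal groups and baseline use unrelated to later use.

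The reach is narrow. Change in medication is neither the primary endpoint (ODI) nor a key secondary endpoint (SF-36, EQol-5D, VAS). It is in none of the three hypotheses and plays no part in the sample size. This overlap leaves those endpoints untouched. It is worth correcting because a stated rule, applied as written, would mislead on a named outcome and the correction is nearly free.

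**What to change.** Add one sentence to Statistical Analysis, Outcomes: the model for change in medication omits pharmacological co-interventions, both as main effects and as interactions with treatment, and keeps baseline medication as the only drug covariate. Drug use after the start of treatment then enters that model only through the outcome. In the worked example this restores -0.20, and in the simulated drug-score model -0.50. It needs no new data, no change to the sample size and no change to the other models.

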#### Effect modification

Possible effect modifiers are all co-interventions, as well as all demographic and baseline characteristics [23,38-40], which include gender [41], age [42], severity of pain [43], comorbidity [44], socioeconomic status [45], work-related factors [34,46,47], indirect reward parameters due to the health care system [48], psychosocial distress [49-52], somatisation and depression [53,54], fear-avoidance beliefs and coping strategies [55,56], and expectations [57].

#### Cost-utility

The socioeconomic objective of the study is to evaluate the cost-utility outcomes of surgical and conservative treatment of CLBP [8,9,27]. The costs considered include the direct health care expenditures borne by the health care system (insurance, public health care) and out-of-pocket expenditures by patients (medication, alternative medicine, personal prevention activities). The indirect social costs due to lost productivity because of absenteeism also will be accounted for [58]. Direct medical costs will collected from health insurance companies in CH, the NHS in NZ and the clinics in which the patients are selected. Indirect costs and out-of-pocket costs will be measured with a cost diary developed by the Zurich University of Applied Sciences in cooperation with the MEM Research Center. The cost diary will be kept by the patients on a weekly basis covering the total period of treatment with a maximum of six months. At beginning of treatment and end of follow-up period utility will be measured with an index based on EQol-5D and SF-36. Changes in the index will be translated into changes in QALYs.

The cost study of CLBP patients will concentrate on the segment of high-cost patients and address this question: Is this group homogeneous with respect to their socioeconomic status, care-seeking and back pain patterns? If the answer is no, are there subgroups whose cost may be reduced substantially by appropriate (nonmedical) support?

The cost-utility part of the study will be done in collaboration with the Zurich University of Applied Sciences, Institute of Health Economics.

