#### Hypotheses

Three hypotheses will be examined:

1. Differences across health care systems result in better treatment outcomes of surgical and conservative treatment of CLBP in countries with a NHS.

2. Patient characteristics, such as high job satisfaction and short pain duration, and co-interventions, such as cognitive behavioural therapy and return-to-work programs, increase the effectiveness of surgical and conservative treatment for CLBP.

3. Cost-utility in terms of quality-adjusted life years (QALYs) is higher in conservative than in surgical treatment of CLBP.

Previous inconclusive findings may have resulted from potential effect modifiers that varied across different health care systems. For instance, expectations to return quickly to work may function as an effect modifier depending on the health compensation system. This study will examine whether the results pertaining to hypotheses 2 and 3 vary by health care system.

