#### Study design

In this multinational prospective cohort study, patients will be recruited consecutively from orthopaedic spine units, rehabilitation centres, and pain clinics in Switzerland (CH) and New Zealand (NZ). Participants will be assessed pre-intervention and at six-month follow-up. The duration of treatment will be a maximum of six months per patient.

The study protocol has been approved by the Ethics Commission of the Canton of Berne (KEK-Gesuchs-Nr.: 191/07).

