#### Costs

The most important cost predictors (including cost drivers) for total, direct, and indirect costs are identified by multivariate modelling approaches.

One multivariate modelling approach is to determine which individuals with CLBP are in the top, say, 15% of the total cost, and to contrast this group with the remaining individuals. The relevant cost predictors are identified by discriminant analysis, or any other suitable classification method such as logistic classification or classification trees.

Another approach is to model the costs by a multiple regression type model, where the costs are assumed to be log-Gaussian or gamma distributed. The uncertainty in the prediction of cost will be quantified by state-of-the-art methods [59,60].

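### The cost diary follows each patient's treatment period while utility covers six months, so the Hypothesis 3 comparison is open to bias if treatment length differs between groups

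*Protocol article*

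**What the plan says.** All references are to the protocol article.

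- **Aim.** Hypotheses, item 3: "Cost-utility in terms of quality-adjusted life years (QALYs) is higher in conservative than in surgical treatment of CLBP". The same section plans to examine whether this result varies by health care system.
- **Cost instrument.** Cost-utility: "Indirect costs and out-of-pocket costs will be measured with a cost diary". The diary is "kept by the patients on a weekly basis covering the total period of treatment with a maximum of six months".
- **Length of treatment.** Study design: "The duration of treatment will be a maximum of six months per patient". Assessments are before the intervention and at six months.
- **Utility.** Cost-utility: "At beginning of treatment and end of follow-up period utility will be measured with an index based on EQol-5D and SF-36". Then: "Changes in the index will be translated into changes in QALYs".
- **Index.** Demographic and baseline characteristics describes the measure as "cost-utility of treatment (index based on EQol-5D in combination with cost data"), and the Methods part of the Abstract likewise names only the EQol-5D. The Cost-utility section adds the SF-36.
- **Other data on absence.** Outcome measures lists duration of work-absenteeism among the secondary outcomes, without linking it to costing.
- **Use of total cost.** Statistical Analysis, Costs, contrasts patients in roughly the top 15% of total cost with the rest.

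**The concern.** A cost-utility comparison needs costs and effects over the same period. Here the effect side has a fixed end, six months for everyone, while the diary side ends when the individual's treatment ends. A patient who finishes treatment early but stays off work, or keeps paying for medication or alternative medicine, contributes six months of utility and a shorter run of diary costs.

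Hypothesis 3 contrasts two kinds of treatment. If treatment tends to end sooner in one of them, the unrecorded cost is larger on that side and the contrast shifts for a reason unrelated to true cost. The same applies between countries if treatment length differs between them, and to the high-cost classification, where longer treatment by itself adds recorded cost.

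Utility raises a second, separate limitation. With two measurements, patients who reach the same six-month value by different routes get the same QALY change, and the routes may differ between surgical and conservative care.

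Data that were never collected cannot be restored at analysis, so the collection window has to be settled in the protocol.

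**Working it through.** The protocol states no cost, utility, QALY or treatment-length figure, so there is no figure of the plan to reproduce. The check sets the windows side by side and then shows, with assumed values, how the mechanism works.

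**1. Windows as written**

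| Component | Start | End | Section |
|---|---|---|---|
| Indirect and out-of-pocket cost (diary) | start of treatment | end of treatment, capped at six months | Cost-utility |
| Treatment | – | varies, at most six months | Study design |
| Utility | beginning of treatment | end of follow-up, six months | Cost-utility, Study design |

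The diary and utility windows coincide only for patients treated for the full six months. Nothing extends the diary for the others.

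**2. Diary weeks lost (treatment lengths assumed)**

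With six months taken as 26 weeks and treatment lasting w weeks, weeks outside the diary = 26 − w.

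- w = 4: 22 weeks lost
- w = 8: 18 weeks lost
- w = 12: 14 weeks lost
- w = 20: 6 weeks lost
- w = 26: 0 weeks lost

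Suppose that true weekly diary cost is the same in both groups and constant over time. The spurious difference, in weeks of cost, is then the difference in treatment length:

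- 8 versus 26 weeks: 26 − 8 = 18
- 12 versus 26 weeks: 26 − 12 = 14
- equal lengths: 0

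The sign depends on which group has the shorter treatment, which the documents do not say.

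**3. Two-point utility (utilities assumed)**

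Take utility 0.40 at baseline and 0.60 at six months (0.5 year). QALY gain = area under the utility curve − 0.40 × 0.5. All paths below share these endpoints.

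- Straight line: 0.5 × (0.40 + 0.60)/2 − 0.20 = 0.050
- Full recovery by week 6: (6/52) × 0.50 + (20/52) × 0.60 − 0.20 = 0.088
- No change until week 20, then linear: (20/52) × 0.40 + (6/52) × 0.50 − 0.20 = 0.012
- Dip to 0.20 at week 4, recovered by week 12: (4/52) × 0.30 + (8/52) × 0.40 + (14/52) × 0.60 − 0.20 = 0.046
- Dip to 0.20 at week 4, linear to week 26: (4/52) × 0.30 + (22/52) × 0.40 − 0.20 = −0.008

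The same two measurements are thus compatible with gains from about −0.01 to 0.09 QALY under these assumptions. Any formula that uses only the change in the index gives one value for all five paths.

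**4. Index**

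Two places base the index on the EQol-5D alone; the Cost-utility section bases it on the EQol-5D and SF-36. The text does not say how the two instruments combine or which one serves Hypothesis 3.

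**The case against.** The strongest reply is that treatment may not end early. The section on conservative treatment and co-interventions defines conservative care as the absence of surgery and lets both groups receive the same co-interventions, including medication and exercise therapy. Treatment then has no obvious end in either group, and many diaries may run to the six-month cap. This stands as a limit on the claim: if everyone is treated for six months, the diary problem vanishes. It also shows that the end of the diary is undefined, which a fixed window would settle.

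Several stronger readings are tempting, but the documents do not support them.

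- **That the comparison is biased, perhaps enough to change its sign.** No treatment length by group is given, so only openness to bias can be shown. The illustrative numbers are not evidence of effect size; one dip-and-recovery path gives 0.046 against 0.050 for the straight line.
- **That the diary is the only information on absence.** Duration of work-absenteeism is also a secondary outcome and might recover part of the productivity loss. The text does not link it to costing, and it does not cover out-of-pocket spending.
- **That the plan assumes a straight line between the two utilities.** It says only that index changes become QALY changes. The formula may stand in a fuller document; the two-point schedule is what limits it.
- **That the cost models undermine Hypothesis 3 because they do not admit zero costs.** The passage "where the costs are assumed to be log-Gaussian or gamma distributed" concerns cost predictors and is one of several approaches there; it is not the surgical-versus-conservative comparison.
- **That direct medical costs share the defect, or that a longer horizon is claimed.** Direct costs come from insurers, the NHS and clinics and are not tied to the diary. No horizon beyond six months is stated.

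**Conclusion.** The point holds in limited form. As written, diary costs and QALYs cover different periods whenever treatment ends before six months, and nothing else in the protocol article repairs this. Hypothesis 3 and the top-15% cost classification are open to bias if treatment length differs between the groups compared. Size and direction cannot be derived from the documents. In the illustration with equal and constant weekly costs, the spurious difference is 0 weeks of cost when lengths are equal and 18 weeks at 8 versus 26.

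The two-point utility schedule is a lesser, independent limitation that remains even if everyone is treated for six months. The differing descriptions of the index are an inconsistency to reconcile. The primary ODI endpoint is unaffected. The change is worth making because it is cheap and the missing diary data could not be recovered later.

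**What to change.** 1. State that every patient keeps the cost diary for a fixed six months from baseline, regardless of when treatment ends. Diary costs and utility then share one window, and no diary weeks are lost by design in either group.
2. Preferably, add the EQ-5D at interim points in that diary and compute QALYs as the area under the utility curve.
3. Reconcile the utility index across the Abstract, the baseline list and the Cost-utility section, and name the one that serves Hypothesis 3.

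The cost is some added patient burden: longer diary keeping for patients who finish treatment early, and a short questionnaire at the interim points. The diary itself is already in use, and the wording change is a few sentences.
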